### Study setting and site selection (SPIRIT point 9)

The study settings are public hospitals in the Free State Province, South Africa. From the total population of 28 hospitals that could be selected as comparators, one was eliminated (Pelonomi Regional Hospital) because it was the site of the Stigma Score Pilot Study.

In order to ensure an equal distribution of large and small hospitals across the different districts in both intervention and control arms, hospitals of similar size (based on numbers of staff), and where possible in the same district, were deliberately paired. Within these pairs, a coin toss was used to randomly allocate hospitals to Arm A or Arm B, and then again to allocate the two arms to intervention or control. The number of hospitals required was estimated considering the fact that the number of staff members across the hospitals in each group differ. The average number of staff members per hospital considered is 220. The same parameters were used as those used to calculate the sample (described later), and the number of hospitals required was estimated to be approximately four hospitals per group (intervention / control). A full list of the sites appears in the addenda (Additional file 2).

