#### Sampling (SPIRIT point 14)

The parameters used for sample size calculation were estimated from the Stigma Score Pilot Study. The mean stigma score considered for the control group was 0.85 with a standard deviation of 0.71. The stigma score is expected to be reduced by approximately 24% to 0.65 in the intervention group with a standard deviation of 0.39. The two-tailed test is considered with Type I error of 0.05 and Type II error of 0.10, to give 90% power. The coefficient of variation considered for each group is 0.25 and the intra-cluster correlation coefficient is 0.05. The estimated sample size per arm is 173 and the estimated inflation factor (design effect) is 1.7. Therefore, the required sample size for this study per arm is approximately 173 × 1.7 ≈ 292 participants. The total number of participants required for this study is 584 (347 respondents in intervention sites and 237 in control sites).

The same HCWs participate in baseline and the post-intervention surveys. Based on our extensive experience of fieldwork in Free State hospitals [32], we estimate that the baseline survey will need 50% oversampling of respondents to allow for loss-to-follow up between baseline and post-intervention surveys (SPIRIT point 15). In practice, a random sample of 882 HCWs was drawn from three broad job categories: *healthcare professionals* (446) (physicians, nurses, and allied HCWs such as psychologists, pharmacists, etc.); *management and administrative staff* (116); and *support staff* (318) (e.g. messengers, cleaners, porters, housekeeping, catering, security, etc.). Two respondents did not indicate their job category.

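### The design effect of 1.7 and the four hospitals per arm do not follow from the stated ICC of 0.05; the protocol's own unadjusted calculation gives about 38–50% power, not 90%

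*Protocol article*

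**What the plan says.** The inputs and results are in the protocol article, Sampling (SPIRIT point 14):

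- Control group: "The mean stigma score considered for the control group was 0.85 with a standard deviation of 0.71".
- Intervention group: "reduced by approximately 24% to 0.65 in the intervention group with a standard deviation of 0.39".
- Error rates: "The two-tailed test is considered with Type I error of 0.05 and Type II error of 0.10, to give 90% power".
- Clustering: "The coefficient of variation considered for each group is 0.25 and the intra-cluster correlation coefficient is 0.05".
- Base size and inflation: "The estimated sample size per arm is 173 and the estimated inflation factor (design effect) is 1.7".
- Result: "the required sample size for this study per arm is approximately 173 × 1.7 ≈ 292 participants". The total is 584, split 347 in intervention sites and 237 in control sites. A 50% oversample is added for loss to follow-up, and 882 staff were drawn in practice.

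The number of clusters is in Study setting and site selection (SPIRIT point 9). Whole hospitals were paired by size and, where possible, district, then allocated by coin toss. The section says the sample-size parameters were used again to find the number of hospitals. It gives the hospital size as "The average number of staff members per hospital considered is 220" and concludes that "the number of hospitals required was estimated to be approximately four hospitals per group (intervention / control").

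The quantitative analysis section plans a linear mixed model of change in stigma between arms, with a random effect for the correlation between a person's two measurements.

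**The concern.** In a cluster-randomised trial the design effect depends on the ICC and the number of respondents per cluster. The article states the ICC, the total sample and the number of hospitals, so the design effect can be checked. A factor of 1.7 looks far too small for an ICC of 0.05 with several dozen respondents in each hospital.

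If so, the 90% power claim does not hold on the protocol's own inputs. Surveying more staff in the same hospitals would help little, because the number of hospitals is what limits precision. A non-significant result read against a stated 90% power could be taken as good evidence that the intervention does not work, when the trial may have had much less chance of detecting the planned reduction.

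**Working it through.** **1. Base sample size (reproduces).** Sum of variances: 0.71² + 0.39² = 0.5041 + 0.1521 = 0.6562. Difference: 0.85 − 0.65 = 0.20.

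n per arm = (1.960 + 1.282)² × 0.6562 / 0.20² = 172.4, rounded up to 173, as stated. So the method was a normal-approximation comparison of two means with no baseline adjustment. Then 173 × 1.7 = 294, close to the stated 292.

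**2. What 1.7 implies.** Design effect = 1 + (m − 1) × ICC. Setting this to 1.7 with ICC 0.05 gives m = 1 + 0.7/0.05 = 15 respondents per hospital, and 292/15 ≈ 19.5 hospitals per arm. If 0.25 is the variation in cluster size, m is about 14. The article does not state 15; it is only what 1.7 implies.

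**3. Design effect for the actual design.** Average m = 584/8 = 73 (347/4 = 86.75 per intervention hospital, 237/4 = 59.25 per control hospital).

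- Design effect = 1 + 72 × 0.05 = 4.6.
- If 0.25 is the variation in cluster size: 1 + (1.0625 × 73 − 1) × 0.05 = 4.83.
- Effective sample size = 292/4.6 = 63 per arm, against 173 needed.
- A design effect of 1.7 at m = 73 would need ICC = 0.7/72 = 0.0097, about a fifth of the stated value.

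**4. Power of the unadjusted comparison.** At m = 73, SE = √(0.6562 × 4.6/292) = 0.1017 and 0.20/0.1017 = 1.967. Normal power = Φ(1.967 − 1.960) = 50%. The t column uses a noncentral t with 2 × (4 − 1) = 6 df.

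| Scenario, four hospitals per arm, ICC 0.05 | Normal | t, 6 df |
|---|---|---|
| 73 per hospital | 50% | 38% |
| 73 per hospital, cluster-size variation 0.25 | 48% | 37% |
| Stated 347/237 split | 49% | 37% |
| All 882 retained (110 per hospital) | 53% | 40% |
| 220 per hospital | 56% | 43% |
| Unlimited respondents | 60% | 46% |

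The last row is the ceiling. As m grows, the effective size per arm tends to 4/0.05 = 80, and SE tends to √(0.6562 × 0.05/4) = 0.0906.

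**5. Number of hospitals.** At m = 220 the design effect is 1 + 219 × 0.05 = 11.95. Hospitals per group = 173 × 11.95/220 = 9.4, so about 10, not four. With no limit on respondents, 172.4 × 0.05 = 8.6 per group would still be needed.

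**6. Difference detectable with 90% power, unadjusted, m = 73.** Normal: 3.242 × 0.1017 = 0.33, or 39% of 0.85. With t on 6 df: 0.40, or 47%. The planned reduction is 0.20, or 24%.

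**7. Allowing for baseline adjustment (assumed correlations).** The article gives none. Assume a person autocorrelation of 0.5 and a cluster autocorrelation of 0.5 to 0.9. The correlation between baseline and follow-up arm means is then

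r = (73 × 0.05/4.6) × cluster autocorrelation + (0.95/4.6) × 0.5,

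which is 0.50 at the low end and 0.82 at the high end. Multiplying the variance by 1 − r² (0.75 and 0.33) gives power of 62% to 93% (normal) or 48% to 81% (t, 6 df).

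**The case against.** The strongest objection is that 38–50% is not the power of the analysis the trial will run. The same staff are surveyed twice and a linear mixed model is planned, so baseline information should add precision. This stands. A reader might infer from the unadjusted figures that the trial cannot detect the planned effect, or that power stays below 90% under any analysis. The document supports neither. Under the assumptions in step 7 the normal approximation reaches 93% at the favourable end; only with the t reference does the whole range stay below 90%. Still, the published calculation claims no gain from baseline and states no correlation, so the mixed model does not rescue the 90% as derived.

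Second, hospitals were randomised within pairs, so 6 df is not the only possible reference. A pair-matched analysis has 3 df, and if pairing removes no variance its unadjusted power is about 28%. This too stands: the degrees of freedom should match the analysis chosen.

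Third, a reader might infer that the 0.25 contradicts the ICC. That requires reading it as a between-hospital coefficient of variation. The article does not say what it measures, and the site-selection section's remark that staff numbers differ between hospitals favours variation in cluster size. On that reading there is no contradiction. Neither reading restores 90%.

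Finally, 73 is an average and 15 is inferred. Both are true, but the stated 347/237 split changes power by only about one percentage point.

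**Conclusion.** The point holds as a contradiction among printed figures. It does not rest on detail that a full protocol or analysis plan might supply. With the stated ICC of 0.05, neither the factor of 1.7 nor four hospitals per group follows. The design effect is understated by a factor of about 2.7 (4.6/1.7).

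The power conclusion rests on the stated means, SDs and ICC, four hospitals per arm, equal average cluster sizes and an unadjusted comparison. On those terms the 90% claim is wrong, and oversampling within the same eight hospitals cannot restore it. Power under the planned pre/post model may be higher, but it cannot be determined from the article. The correction matters because it governs how a null primary comparison should be read.

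**What to change.** Keep the eight hospitals, and amend the two sections as follows:

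- Replace 1.7 by 1 + (m − 1) × ICC with the actual number of respondents per hospital: 4.6 at 73, or 1 + 109.25 × 0.05 = 6.5 if all 882 (about 110 per hospital) are retained. If the 0.25 is variation in cluster size, use the form that includes it.
- Withdraw the 90% power statement and the statement that about four hospitals per group follow from the same parameters. Give the number of hospitals as a fixed feature of the design.
- Restate the power for a 0.20 difference, and the detectable difference, for the planned mixed model. State the assumed person and cluster baseline correlations with a range, and use a small-sample reference whose degrees of freedom match the analysis (6 if unpaired, 3 if pair-matched). Show the unadjusted detectable difference of about 0.33 to 0.40 alongside.
- Say what the coefficient of variation of 0.25 measures and how it enters the calculation.

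The cost is recalculation and rewording, and a less favourable stated power. No participants or hospitals are added.

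### The sample size calculation requires 292 per arm, but the stated split is 347 intervention and 237 control; at the plan's own SDs and design effect this gives about 86 to 87.5% power, not 90%.

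*Protocol article*

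**What the plan says.** All the inputs are in the Sampling section of the protocol article.

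- Control arm: "The mean stigma score considered for the control group was 0.85 with a standard deviation of 0.71".
- Intervention arm: the score is expected to be "reduced by approximately 24% to 0.65 in the intervention group with a standard deviation of 0.39".
- Error rates: "The two-tailed test is considered with Type I error of 0.05 and Type II error of 0.10, to give 90% power".
- Clustering: "The coefficient of variation considered for each group is 0.25 and the intra-cluster correlation coefficient is 0.05".
- Unadjusted size and inflation: "The estimated sample size per arm is 173 and the estimated inflation factor (design effect) is 1.7".
- Result: "the required sample size for this study per arm is approximately 173 × 1.7 ≈ 292 participants".

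The next sentence reads: "The total number of participants required for this study is 584 (347 respondents in intervention sites and 237 in control sites". The section then adds 50% oversampling at baseline, explicitly to cover loss between the two surveys, and reports a baseline sample of 882. The 584 is therefore the number wanted after loss. How the 882 divide between the arms is not given.

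**The concern.** Two consecutive sentences disagree. One fixes a requirement for each arm. The next keeps the total but moves 55 people from control to intervention, a ratio of 347/237 = 1.46 to 1 that the formula did not use.

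The direction matters because the plan assumes unequal SDs. The control arm contributes 0.5041 of the summed variance of 0.6562 (77%), so a shortfall there costs more than the same shortfall in the other arm. As written, 237 controls would count as satisfying a 90% power requirement that they do not satisfy on the plan's own figures.

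**Working it through.** **Inputs** (Sampling section): difference 0.85 − 0.65 = 0.20; SD 0.71 control and 0.39 intervention; two-sided 5% (z = 1.960); 90% power (z = 1.2816); design effect 1.7. Four hospitals per arm come from the section on study setting and site selection.

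**Step 1: reproduce the plan's figure.**
n per arm = (0.71² + 0.39²)(1.960 + 1.2816)² / 0.20² = 172.4, rounded up to 173, as stated. 173 × 1.7 = 294.1 (172.4 × 1.7 = 293.0) against the printed 292; the difference is rounding and does not matter. The formula assumes equal arms.

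**Step 2: power at 292/292.**
Variance of the difference before inflation = (0.5041 + 0.1521)/292 = 0.002247.
Power = Φ(0.20/√(1.7 × 0.002247) − 1.96) = 89.9%. This agrees with the stated 90%.

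**Step 3: power at 347 intervention and 237 control.**
Variance = 0.1521/347 + 0.5041/237 = 0.002565, larger by a factor of 0.002565/0.002247 = 1.14.
Power = Φ(0.20/√(1.7 × 0.002565) − 1.96) = 85.7%. The type II error is about 0.14 instead of 0.10.

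**Step 4: let the design effect follow cluster size (assumption).**
Fewer controls over the same four hospitals means smaller control clusters: 237/4 = 59.25, against 347/4 = 86.75 and 292/4 = 73 for equal arms. Anchoring 1.7 at 73 per hospital gives (1.7 − 1)/72 = 0.0097 per additional respondent. The design effects are then 1 + 58.25 × 0.0097 = 1.57 (control) and 1 + 85.75 × 0.0097 = 1.83 (intervention).
Power = Φ(0.20/√(1.57 × 0.5041/237 + 1.83 × 0.1521/347) − 1.96) = about 87.5%.

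**Step 5: how much depends on the SDs.**
With a common SD of √(0.6562/2) = 0.573 and design effect 1.7, the 347/237 split gives 88.8%, a loss of about 1 point. Most of the loss in step 3 therefore arises because the short arm is the one with the larger SD.

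**Step 6: controls needed alongside 347 intervention respondents, design effect 1.7.**
n control = 1.7 × 0.5041 / (0.20²/(1.960 + 1.2816)² − 1.7 × 0.1521/347) = 279.9, so about 280.

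**Step 7: what happens if the 1.7 is not accepted.**
The stated intra-cluster correlation of 0.05 and a design effect of 1.7 together imply 1 + 0.7/0.05 = 15 respondents per hospital, whereas 584/8 = 73. At 73 the design effect is 1 + 72 × 0.05 = 4.6, and power at 292/292 is 50.3%. At 347/237, with design effects of 5.29 (intervention) and 3.91 (control) from the arms' own cluster sizes, it is 49.2%. The split then costs about 1 point. Forcing 4.6 on both arms would give 45.3%, but that ignores the different cluster sizes.

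**The case against.** Several points on the other side have force.

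- **The size is conditional.** The 86% holds only under a common design effect of 1.7, which is hard to square with the stated intra-cluster correlation. Scaling it by arm reduces the loss from 4.2 to about 2.4 points. This stands, and the size should be given as a range with its condition.
- **The SDs are planning values.** With equal SDs the loss is about 1 point. This also stands, but the plan chose those SDs and rests its 173 on them.
- **The calculation is not the planned analysis.** The Data analyses section plans a linear mixed model on two measurements per person. The figures here test the plan's own sample size statement. A reader might infer that the trial will have 86% power; the documents do not establish that.
- **More people were surveyed.** All 882 baseline respondents are to be followed up, and nothing makes 237 a stopping point. A reader might infer that the control arm will end 55 short; that is unknown, because the baseline split is not given. Still, the oversampling is assigned to loss. If the 882 divided in the same ratio (assumption), there would be about 358 controls, and the planned retention of 584/876 = 67% would leave about 239.
- **Hospital sizes may explain the ratio.** A reader might infer that 1.46 to 1 contradicts the aim of pairing hospitals by size ("In order to ensure an equal distribution of large and small hospitals across the different districts in both intervention and control arms"). The documents do not support that. Pairs were of similar size, not equal size, a ratio of respondents is not a ratio of hospital sizes, and the site list is in an additional file that is not shown. Equally, the article offers no such reason for these numbers, and a reason would not restore the power.

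**Conclusion.** The statement is wrong as written: the printed allocation does not meet the printed per-arm requirement or deliver the printed power. On the plan's SDs and design effect of 1.7, power at 347/237 is 85.7% with a common design effect and about 87.5% with one scaled to each arm's cluster size, against 89.9% for equal arms.

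The shortfall is modest, roughly 2 to 4 points. It is not the main threat to power: if the design effect is rebuilt from the stated intra-cluster correlation, power is near 50% and the split explains only about 1 point. Correcting the design effect would nevertheless leave the contradiction between 292 per arm and 347/237 in the text, so it needs its own correction.

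**What to change.** 1. Replace the 90% power statement with the power recalculated for 347 and 237, stating the design effect used in each arm. If the split is a misprint, correct it.
2. Do not describe 237 controls as meeting the 90% requirement. At design effect 1.7 and 347 intervention respondents, about 280 controls are needed.
3. Give the reason for the unequal split in one sentence.
4. Report precision for the arm sizes actually followed up in the 2018 survey.

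The cost is wording and one recalculation. No new participants are asked for, and follow-up of every baseline respondent is already planned. Wording cannot secure more controls: on the assumed 358 baseline controls, reaching 280 would need about 78% retention (280/358), above the 67% planned. Stating the true power and reporting the achieved precision is therefore the part that can be guaranteed.

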#### Recruitment (SPIRIT point 15; see also Section 3.3.1)

Over its long history of working in Free State public health facilities, the CHSR&D has developed effective mechanisms to recruit participants. We begin by consulting closely with provincial managers and then proceed to consult with individual hospital CEOs; these communications aim to make sure that the study and its details are properly communicated to the relevant top managers. The CEOs then generally call a meeting of other managers operating at all levels throughout the facility. At this crucial meeting we present the research and explain what is required to support it, including the number and distribution of staff required to participate. They then advise on best recruitment processes. Recruitment always requires research fieldworkers—as well as implementers—to be very flexible and sometimes work after hours in order to accommodate staff on different shifts, and allow for the relative time and workload pressures experienced in different jobs and in different types of wards.

Fieldworkers are very well trained and sensitised to ethical protocols and practices. Each one is given a list of the randomly selected participants who he/she needs to locate, approach with introductory information about the research, and invite to participate. Finding selected candidates usually entails working through ward managers or matrons, line managers and supervisors. People who are willing are then taken through the full informed consent process by the fieldworker, and can opt to do this in one of three local languages (English, Sesotho, or Afrikaans). If the fieldworker is not proficient in the person’s language of choice, he/she will hand the participant over to a fieldworker who is. Fieldworkers can easily contact one another or the on-site fieldwork manager/s, as they all carry cell phones with airtime.

Fieldworkers attempt to contact persons on their list at least three to four times. Where the potential participant is on leave or off sick for the duration of the data collection in that hospital, or if they do not agree to participate, the fieldworkers proceed systematically through their list of randomly selected replacement candidates. These processes are repeated until the required sample of participants for the surveys is obtained.

Although the *processes* described in this section are similar for recruiting survey respondents and intervention participants, the latter are not sampled in the same way. Selection for interventions is described in the next section.

## Interventions (SPIRIT point 11a)

It is accepted—particularly in prevention science—that a combination of interventions is more effective at bringing about desired change than a single intervention [33–35]. Thus, a mix of interventions— *clinical*, *structural*, and the most important, *socio-behavioural*—is proposed for simultaneous rollout. Interventions are informed by insights from key publications [24, 36–39]. Stigma-reduction activities also target three communication levels—*individual, community, and socio-structural*.

As indicated in the ‘Background’ section, interventions are based on a comprehensive review of the academic literature—particularly literature on stigma as it relates to HCWs—including our own preliminary studies on issues that impact stigma in FSDoH workplaces [17, 18, 30], and piloting of social marketing materials [30].

### The clinical intervention

This is being implemented by [name]—a physician with the Free State Department of Health (FSDoH) and a member of the research team. She will support occupational health (OH) nurses—and, where OH units do not exist, staff physicians and nurses who test and treat facility staff for HIV and TB—to provide screening and treatment for TB and human immunodeficiency virus (HIV)/acquired immune-deficiency syndrome (AIDS). This is already part of her work, so the project ‘piggy backs’ on her efforts in this regard. What is extra is that she will also assist with any issues and questions that arise from the stigma-reduction workshops for HCW change agents (described below).

Because we might not get physicians to attend the workshops, and because as a physician she is perfectly positioned to be heard by her professional peers, she will promote awareness of HIV and TB stigma among physician in intervention sites via a PowerPoint presentation at one of their monthly clinician’s meetings.

